#### Patient background and secondary endpoints

Summary statistics will be obtained for each group. Continuous variables will be summarized by mean and standard deviation or median and interquartile range. Categorical variables will be summarized by frequency and proportion.

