### Objectives {7}

The objective is to determine whether preoperative INI administration reduces the incidence of POD in elderly patients undergoing cardiac surgery requiring cardiopulmonary bypass. In addition, the effects on cognitive function in the early postoperative period will be evaluated.

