### Sample size {14}

In a study conducted at the University of Yamanashi Hospital, 33% of patients were in the placebo group and 9.5% in the insulin group (unpublished data, jRCTs031200290). Although that previous study differs from the present study in that it excluded patients aged 20 years or older undergoing cardiac or major vascular surgery using cardiopulmonary ventilation and patients with severe renal dysfunction, the incidence of delirium seems reasonable.

Based on this, if the delirium rates in the placebo and insulin groups are 33% and 10%, respectively, with two-sided a significance level of 0.05 on both sides and a power of 0.8, the number of cases per group would be 49. We will recruit 55 cases per group for a total of 110 cases, taking into account 10% dropout cases.

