## Statistical methods

### Statistical methods for primary and secondary outcomes {20a}

#### Primary endpoint

The incidence of delirium within the first postoperative week for each group will be determined. The ratio of the incidence rate in the insulin group versus the placebo group and its 95% confidence interval will be determined.

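### The effect on early cognitive function is an objective, but the stated analysis of MMSE-J and MoCA-J gives only per-arm summaries, with no between-group estimate or interval

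*Protocol article*

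**What the plan says.** Objectives {7} names delirium first and then adds a second aim: "In addition, the effects on cognitive function in the early postoperative period will be evaluated". The Discussion also treats cognitive function as an outcome alongside delirium.

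The list of secondary endpoints under Outcomes {12} defines the cognitive endpoints as the change in MMSE-J and the change in MoCA-J from before surgery to postoperative day 7. Plans for assessment and collection of outcomes {18a} has both tests recorded at enrolment and again after surgery.

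Statistical methods for primary and secondary outcomes {20a} has two parts. For the primary endpoint: "The ratio of the incidence rate in the insulin group versus the placebo group and its 95% confidence interval will be determined". For patient background and secondary endpoints, taken together: "Summary statistics will be obtained for each group", followed by "Continuous variables will be summarized by mean and standard deviation or median and interquartile range". Categorical variables get frequencies and proportions. Nothing further is stated for the cognitive scores.

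**The concern.** In a randomised trial an effect is a contrast between arms. The article states such a contrast, with its precision, for delirium. In the same section it states a purely descriptive method for the endpoints that carry the cognitive objective, the same method as for age or comorbidities. An analysis that followed this text would report two columns of numbers and no estimate of what insulin did to cognition.

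Two things are at stake. First, no estimator is fixed in advance, so whether to compare change scores, day-7 scores or adjusted scores could be settled after the data are seen. Second, readers will compare the two mean changes by eye, and that comparison is less precise than the baseline-adjusted one that the same data allow.

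**Working it through.** **1. The plan's own figure.** Sample size {14} assumes "if the delirium rates in the placebo and insulin groups are 33% and 10%, respectively", two-sided 0.05, and "a power of 0.8, the number of cases per group would be 49". With pooled variance and mean rate (0.33 + 0.10)/2 = 0.215:

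n = [1.96·√(2·0.215·0.785) + 0.8416·√(0.33·0.67 + 0.10·0.90)]² / 0.23² = (1.139 + 0.469)² / 0.0529 ≈ 48.9, so 49 per group.

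Allowing for 10% dropout, 49/0.9 = 54.4, so 55 per group. Both stated figures reproduce. They concern delirium only and serve here just to supply n.

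**2. Objective against method.**

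| | Delirium | MMSE-J, MoCA-J |
|---|---|---|
| Named in Objectives {7} | yes | yes (cognitive function) |
| Per-arm summary stated in {20a} | yes | yes |
| Between-group estimate stated | yes (ratio) | no |
| 95% CI stated | yes | no |
| Use of baseline | not applicable | through the change score only |

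**3. What the per-arm summaries allow.** If mean, SD and n of the change are reported by arm, a reader can form the difference in means ± 1.96·√(SD₁²/n₁ + SD₂²/n₂). If medians and interquartile ranges are reported, this generally cannot be done. The text allows either.

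**4. What baseline adjustment would add.** The documents give no SD and no baseline to day-7 correlation r for either score, so r is an assumption, shown over 0.3 to 0.8. Assume also that the SD is the same at baseline and day 7, and work in units of that SD.

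- Variance per patient, change score: 2(1 − r)
- Variance per patient, ANCOVA on baseline: 1 − r²
- Ratio: (1 − r²) / [2(1 − r)] = (1 + r)/2
- 95% CI half-width for the difference: 1.96·√(2·variance/n), with n = 49 per group

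| r | Change | ANCOVA | Ratio | Half-width, change | Half-width, ANCOVA |
|---|---|---|---|---|---|
| 0.3 | 1.40 | 0.91 | 0.65 | 0.47 SD | 0.38 SD |
| 0.5 | 1.00 | 0.75 | 0.75 | 0.40 SD | 0.34 SD |
| 0.6 | 0.80 | 0.64 | 0.80 | 0.35 SD | 0.32 SD |
| 0.7 | 0.60 | 0.51 | 0.85 | 0.31 SD | 0.28 SD |
| 0.8 | 0.40 | 0.36 | 0.90 | 0.25 SD | 0.24 SD |

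With 55 per group and r = 0.5 the half-widths are 0.37 and 0.32 SD.

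**5. Effect of the entry cutoff.** The exclusion criteria remove patients with MMSE-J of 23 or less, which can narrow the baseline spread and break the equal-SD assumption. Under a linear model with slope b, residual variance e and baseline variance s, the ANCOVA variance is e and the change-score variance is e + (b − 1)²·s. Selecting on baseline leaves b and e alone and shrinks s. Illustration with assumed values b = 0.5, e = 0.75:

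- s = 1: 0.75 / (0.75 + 0.25) = 0.75, a gain of 25%.
- s = 0.5: 0.75 / (0.75 + 0.125) = 0.86, a gain of 14%.

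So for MMSE-J the gain may be smaller than the table in step 4 suggests.

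**The case against.** The strongest reply is that this is a condensed article. A full protocol is available on request and an analysis plan may exist. Models and covariates usually belong there, and the text does not say that summaries are the only analysis. It can be added that the trial is sized on delirium alone, and that describing secondary endpoints without formal inference is a cautious choice for 110 patients.

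Part of this stands. The absence of ANCOVA is not in itself an error, and descriptive reporting would be defensible if the objective were worded as descriptive. But the section is not silent. It states a method for these endpoints, directly below a between-group ratio with interval for the primary one, and that method does not yield the effect named in the objective.

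A reader might infer more than the documents support:

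- *That the cognitive objective cannot be answered.* Means and SDs by arm would give an unadjusted difference and interval. Only the median and interquartile route generally blocks this.
- *That the baseline scores go unused.* The endpoints are changes from baseline, so baseline enters. The issue is efficiency.
- *That regression to the mean distorts the comparison.* The MMSE-J cutoff applies to both arms before 1:1 randomisation, so it acts equally on each in expectation.
- *That the cutoff makes adjustment more valuable.* Under the linear model above it does the reverse.
- *That a worst-rank analysis of patients untestable on day 7 is required.* That is a matter of preference, and it would have to be reconciled with the rule in {20c} that missing data are not replaced.

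**Conclusion.** The point holds as a mismatch between a stated objective and a stated method. The article sets out to evaluate effects on early cognitive function and then specifies only per-arm summaries for the endpoints concerned, with no between-group estimate or interval.

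A baseline-adjusted difference would close the gap. It would also be about 10% to 35% less variable than the change-score comparison for r from 0.8 down to 0.3. That range rests on an assumed correlation and on equal baseline and day-7 SDs, neither of which the documents give, and for MMSE-J it may overstate the gain because of the entry cutoff. The mismatch itself does not depend on these figures.

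The primary endpoint, its analysis and the sample size are untouched. This is a worthwhile improvement at almost no cost, not a threat to the trial's main conclusion.

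**What to change.** In Statistical methods {20a}, split patient background from secondary endpoints. Keep the per-arm summaries for both, and add for MMSE-J and MoCA-J: the between-group difference in day-7 score with 95% CI, from an ANCOVA with terms for arm, baseline score and hospital (the stratification factor in Sequence generation {16a}), labelled secondary or exploratory.

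The endpoint definitions can stay as changes from baseline. With baseline in the model, analysing the change or the day-7 score gives the same adjusted difference.

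If the investigators want description only, the alternative is to reword the cognitive aim in Objectives {7} accordingly. That removes the mismatch but gives up the estimate.

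The cost is a few sentences and a routine model. Both scores are already collected before and after surgery, and the hospital is known from randomisation, so no new data, visits or patients are needed.

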### Interim analyses {21b*}*

Not applicable. No interim analyses are to be performed because the study period is relatively short, the patient number is small, and the anticipated incidence of severe adverse events will be low. The study will be terminated (i) if it becomes impossible to achieve the planned number of patients due to difficulties in recruiting, (ii) if hypoglycemia occurs frequently in the insulin group, and/or (vi) if the research ethics board recommends study termination.

### Methods for additional analyses (e.g., subgroup analyses) {20b}

Not applicable. There are no subgroup analyses planned because the patient number is relatively small and most of the surgeries will be valve surgery.

### Methods in analysis to handle protocol non-adherence and any statistical methods to handle missing data {20c}

There will be no non-adherence issues in this study because the study drug is administered by the investigator. The possibility of missing values in the primary outcome will be very low because POD is assessed every day for seven days. Missing data will not be replaced.

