**Methods:**

A multicenter, double-blind, randomized, controlled trial will be conducted at University of Tsukuba Hospital and Tsukuba Medical Center Hospital, Japan, from July 1, 2023, to December 31, 2025. A total of 110 elderly patients (65 years old or older) undergoing cardiac surgery requiring cardiopulmonary bypass will be enrolled and randomly allocated to intranasal insulin or intranasal saline groups. The primary outcome is the incidence of POD within 7 days after surgery. Secondary outcomes include days and times of delirium, screening tests of cognitive function, pain scores, duration of postoperative tracheal intubation, and length of ICU stay.

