## Introduction

### Background and rationale {6a}

Postoperative delirium (POD) is a complication after surgery in which acute disturbances of consciousness, attention, and perception appear and show diurnal fluctuations, resulting in impaired attention/thought processes and circadian rhythm disturbances [1]. This syndrome is increasing as more elderly patients undergo major surgery [2, 3]. The frequency is 10–25% [4, 5] but reaches as high as 50% for cardiac surgery [6].

Delirium is a short-term disease concept but has been shown to worsen long-term prognoses with increased lengths of hospital stay, postoperative complications, and mortality [7, 8]. Many patients with POD suffer mid-to-long-term postoperative neurocognitive dysfunction (cognitive dysfunction detected postoperatively in the absence of impaired consciousness using neuropsychological testing) [9], which leads to serious deteriorations in quality of life, such as an inability to work [10]. However, there is no standard prophylaxis for POD because pharmacological interventions, mainly anti-inflammatory, have not shown effective results in preventative treatment [11].

The precise mechanism of POD pathogenesis remains unknown but the neuroinflammatory response theory is the most likely explanation. Systemic inflammation induced by surgery and anesthesia causes acute brain inflammation [12]. In cardiac surgery, strong neuroinflammation is particularly induced by cardiopulmonary bypass (CPB), median sternotomy, myocardial ischemia-reperfusion injury, and various anesthetic agents [6], with these surgical factors thought to contribute to the high rate of delirium.

Intranasal insulin (INI) administration of up to 160 units in patients with cognitive dysfunction and delirium has been shown to improve memory function and brain metabolism [13–16] without hypoglycemia [17]. Glucose-insulin-normoglycemia therapy (high-dose intravenous insulin) [18] preserves short- and long-term memory after cardiac surgery [19] by suppressing inflammation in the brain due to insulin spilling over into the cerebrospinal fluid [20]. Insulin signaling in the brain was associated with cognitive function and perioperative inflammatory responses. Therefore, INI could be exploited to reduce POD and/or cognitive dysfunction.

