## Outcomes {12}

### Primary endpoint

Incidence of delirium within 7 days after surgery. Delirium will be evaluated for 7 days after cardiac surgery. During the intensive care unit (ICU) stay, the Confusion Assessment Methods for the Intensive Care Unit (CAM-ICU) [23, 24] will be conducted twice a day for each patient. In wards, the newly developed 3-min diagnostic assessment for delirium using the Confusion Assessment Method (3D-CAM) [25] will be conducted once a day for each patient.

A patient is considered to have delirium if he/she tests positive for delirium at least once during the postoperative period.

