#### Secondary endpoint

Number of days with deliriumNumber of times the patient has deliriumChange in MMSE-J between preoperative and 7 postoperative dayChange in the Japanese version of Montreal cognitive assessment (MoCA-J) [26, 27] between preoperative day 1 and postoperative day 7Pain score numerical rating score (NRS) [28]Length of postoperative tracheal intubationLength of ICU stay

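### Delirium-day counts give low values to patients who die early or are too sedated to assess, and the day-7 cognitive change drops those who are dead or untestable

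*Protocol article*

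**What the plan says.** All references are to the protocol article.

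- **Outcomes {12}, Secondary endpoint.** Delirium burden is a plain count of days and of times with delirium. Cognition is the change in MMSE-J and MoCA-J from before surgery to postoperative day 7. Intubation and ICU stay are plain lengths. None of these is expressed per day alive or per day assessable.
- **Outcomes {12}, Primary endpoint.** In the ICU, CAM-ICU "will be conducted twice a day for each patient"; on the ward, 3D-CAM is done once a day. No result category is given for a patient who cannot be assessed.
- **Statistical methods {20a}, Patient background and secondary endpoints.** "Summary statistics will be obtained for each group", as mean and SD or median and IQR.
- **Missing data {20c}.** "Missing data will not be replaced". The only comment on how much will be missing concerns the primary outcome: "The possibility of missing values in the primary outcome will be very low because POD is assessed every day for seven days".
- **Objectives {7}.** Early postoperative cognitive function is a stated second aim.

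No section says how death, deep sedation or inability to be tested enters a secondary endpoint.

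**The concern.** Two secondary endpoints respond to a bad course in the wrong way.

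**Delirium days.** A patient who dies early stops accruing days. A patient too sedated for CAM-ICU cannot test positive. Both end with a low count, which reads as little delirium.

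**Day-7 cognition.** The test falls inside the 7-day delirium window. A patient who is dead, sedated or too delirious to cooperate has no score, and under {20c} simply leaves the summary. Those removed are likely to be among the worst performers.

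The trial's own hypothesis makes the second loss unequal: more delirium on placebo means more placebo patients likely to be untestable on day 7. Dropping them makes placebo look better on an outcome named in the objectives, so a real cognitive benefit of insulin could be understated.

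**Working it through.** **1. The plan's own figure.** Sample size {14} states: "if the delirium rates in the placebo and insulin groups are 33% and 10%, respectively", two-sided alpha 0.05, power 0.80, 49 per group. With pooled variance under the null and no continuity correction:

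n = [1.960 × √(2 × 0.215 × 0.785) + 0.842 × √(0.33 × 0.67 + 0.10 × 0.90)]² / 0.23² = (1.139 + 0.469)² / 0.0529 ≈ 48.9, so 49.

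49 / 0.90 = 54.4, so 55. Both figures reproduce. This point does not touch them.

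**2. Day-7 cognition: how many patients.** The documents give no rate of delirium persisting to day 7, so 25% and 50% are assumptions. Number delirious on day 7 = 55 × delirium rate × persistence.

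| Persistence (assumed) | Placebo | Insulin |
|---|---|---|
| 25% | 55 × 0.33 × 0.25 = 4.5 (8.3%) | 55 × 0.10 × 0.25 = 1.4 (2.5%) |
| 50% | 55 × 0.33 × 0.50 = 9.1 (16.5%) | 55 × 0.10 × 0.50 = 2.8 (5.0%) |

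As counts lost through delirium these are upper limits, because they treat every patient delirious on day 7 as untestable. Lower persistence, or more patients who can be tested, shrinks them towards zero.

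**3. Day-7 cognition: shift in the comparison.** Leaving out a fraction f whose true change is d points worse than that of the tested patients raises the arm mean by f × d. The between-arm shift is (f placebo − f insulin) × d. Assuming d = 5 to 10 points:

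- 25% persistence: (0.0825 − 0.025) × 5 to 10 = 0.29 to 0.58 points
- 50% persistence: (0.165 − 0.05) × 5 to 10 = 0.58 to 1.15 points

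The shift favours placebo. With equal loss in both arms it would largely cancel.

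**4. Delirium days.** The documents give no rate of death or deep sedation. Suppose m of 55 patients in an arm would each have had 5 delirium days but record 0 to 2. The arm mean is understated by m × (5 − recorded) / 55:

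- m = 1: 0.05 to 0.09 days
- m = 3: 0.16 to 0.27 days
- m = 6 (about the planned 10% dropout): 0.33 to 0.55 days

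For scale, if a delirious patient has 2 to 3 delirium days (assumed), the planned rates imply a mean difference of 0.23 × 2 to 3 = 0.46 to 0.69 days. Only the difference in understatement between arms biases the comparison, and the documents do not say which arm would have more deaths or deep sedation.

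**5. Ventilator and ICU lengths.** Only early death cuts these short. A survivor who stays sedated would be expected to have longer intubation and ICU stay, so these endpoints show that patient as worse.

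**The case against.** The strongest reply is that much of this is silence. Rules for death and unassessable days commonly sit in a full protocol or SAP, and neither is shown. Secondary endpoints are only to be summarised, with no test stated. Patients are scheduled cases without obvious neurological disease and with MMSE-J above 23, so deaths and untestable patients may be few. The persistence rates and point deficits above are not in the documents. The no-replacement sentence is also not what causes the death problem, because a score after death is undefined and imputation would not repair it. Finally, the cognitive bias runs against the trial's hypothesis, so it would not create a false benefit.

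Most of this limits the weight of the point without removing it. The article does fix the endpoint definitions and a blanket missing-data rule, and any later rule would have to be squared with them. A bias that hides an effect still matters for a stated objective.

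A reader might infer more than the documents support:

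- **That dead, sedated and delirious patients all look well on every secondary endpoint.** Sedated survivors have longer, not shorter, ventilator and ICU times. Patients too delirious for cognitive testing can still be CAM-ICU or 3D-CAM positive and so add delirium days.
- **That a patient who dies on day 2 with two delirium days beats many survivors.** At the planned rates, 67% of placebo and 90% of insulin patients have no delirium day at all, and the article gives no distribution of ICU or intubation time.
- **That testing a delirious patient contradicts the article's own definition.** The Background {6a} phrase, "cognitive dysfunction detected postoperatively in the absence of impaired consciousness using neuropsychological testing", explains mid-to-long-term dysfunction. It does not define the day-7 endpoint, which is a change in screening scores.

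**Conclusion.** The point holds for two endpoints. As written, delirium-day counts give low values to patients who die early or are too sedated for CAM-ICU, and day-7 cognitive change omits the dead and untestable. At the planned delirium rates the cognitive loss is likely to be unequal and to favour the arm with more delirium.

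The size is unknown. With 25-50% persistence to day 7, at most about 4.5-9.1 placebo and 1.4-2.8 insulin patients of 55 are affected. With a further assumed deficit of 5-10 points, the between-arm shift is about 0.3 to 1.2 points at those upper limits, and less if many delirious patients can be tested.

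The effect on ventilator and ICU lengths is confined to early deaths and is probably small. The primary endpoint and the sample size are not affected. This is worth correcting because it bears on a stated objective and is cheap to mend; it does not threaten the main result.

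**What to change.** - **Delirium burden (Secondary endpoint).** Define it over the fixed 7-day window as days alive without delirium or coma, where coma means too sedated for CAM-ICU, recorded at the assessments already planned.
- **MMSE-J and MoCA-J.** Record why a day-7 test was not done. Report by arm the number not tested because of death, sedation or delirium. Keep the score summary for those tested, and show it also for those not delirious on day 7, using the delirium result already planned for that day. That subset is selected after randomisation, so it is descriptive only.
- **Supporting rank comparison.** Give the worst rank only to patients who are dead, or untestable because of sedation or delirium. Tested patients who are delirious keep their own score; giving them the worst rank would count delirium a second time as cognitive loss.
- **Ventilator and ICU lengths.** Report deaths by arm beside them.
- **{20c}.** Reword the no-replacement sentence so that it agrees with these rules.

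The cost is wording plus one extra data item, the reason an assessment could not be done; Plans for assessment {18a} lists neither this nor sedation level. The rank result is harder to read in points, which is why the score summary stays.
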